### 8.1. Aims

To develop and assess the efficacy of DHL interventions on self-protection of COVID-19 and promoting COVID-19 vaccination among EMs, Chinese PWCI and CGs in HK. *Objective 1.* To co-create DHL interventions with these three groups susceptible to COVID-19 and meet their specific needs in DHL to prevent infection. *Objective 2.* To assess the efficacy of the DHL interventions on eHealth literacy, vaccine literacy and actions taken for COVID-19 prevention.

### 8.2. Plan of Investigation

This 4-year research program will consist of three interrelated but independent studies of three specific populations with similar study designs. Study A will target five EMs in HK (Filipinos, Indonesians, Indians, Nepalese and Pakistanis), whilst Study B will target Chinese PWCI and Study C will target CGs (including health workers in residential care homes and family CGs of frail older people). Each study will have three phases. Phase 1 will involve the use of a community-based participatory research approach to involve stakeholders in the development of the interventions; Phase 2 will involve testing the feasibility and acceptability of the interventions; and Phase 3 will involve examining the efficacy of the interventions using a randomised controlled trial design.

#### 8.2.1. Subjects

Phase 1. Thirty EM adults, 30 PWCI and 30 CGs will be recruited for focus group interviews before the development of the interventions begins. Another 10 EM adults (2 from each ethnic group), 10 PWCI and 10 CGs will be invited to participate in cognitive interviews. Phase 2. Twenty EM adults, 20 PWCI, 20 CGs and 6 moderators will be invited to participate. Phase 3. One hundred fifty-six EM adults, 156 PWCI and 156 CGs will be randomised to the intervention or the control group.

We estimated the sample size for the trial of each proposed study based on a previous eHealth Literacy study that reported a small-to-moderate effect size (d = 0.245) [38]. For the proposed study, with five repeated measurements over a 6-month period, a total sample size of 108 subjects (i.e., 54 per group) is required to achieve a power of 90% when using a repeated-measures analysis of variance to detect a significant between-group interaction effect at 5% significance (G*Power 3.1). Furthermore, assuming an attrition rate of 30% [39], 156 subjects (78 per group) will be recruited for each study.

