#### 8.2.3. Study Design

Phase 1. Each qualitative study will include three to five focus group interviews and five cognitive interviews. In the focus group interviews, the stakeholders will be encouraged to indicate their problems and concerns about DHL, propose resources/solutions and formulate a plan. Version 1 of the interventions will be based on these comments. Cognitive interviews will be conducted with the stakeholders when the version 1 interventions are available. Here, we will ask the stakeholders to go through the interventions step-by-step to evaluate their flow and content.

Phase 2. A feasibility and acceptability study with individual interviews will be conducted to collect views from 20 stakeholders and two moderators. The moderators will be the trained workers who facilitate online group discussions on social media platforms.

Phase 3. This will be a two-arm, prospective, parallel-group (1:1), randomised controlled trial.

Settings. Participants will be recruited from non-governmental organisations that provide services to EMs, PWCI and CGs.

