Data analysis. Phases 1 and 2. The qualitative data analysis will occur in two steps. In the first step, a researcher will read through the transcripts and develop a codebook with definitions. Another researcher will then review the transcripts and add emergent codes as appropriate. The codebook and the definitions will be refined via discussion between the academic researchers and stakeholders. The second step of the analysis will focus mainly on the identification of themes and subthemes and on obtaining consensus across the team. Phase 3. To examine between-group differences in changes in the outcomes, we will perform separate linear mixed-effects models for each of the continuous outcomes (eHEAL, DHLI, vaccine literacy, knowledge, attitudes, and practices towards COVID-19) and three independent variables: ‘Time’, ‘Group’ and their interaction term ‘Time × Group’. A significant result of the interaction term (Time × Group) will indicate a differential change in the outcome variable between the two groups.

## 9. Study 3

#StayOkayHK: A universal public health initiative to promote stay-at-home during COVID-19

This project will develop and test a novel universal public health initiative (#StayOkayHK), incorporating a public health communication campaign, health education and promotion, and participatory social media strategies to encourage the HK public to stay at home to reduce the risk of SARS-CoV-2 transmission.

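### Study 2: 108 evaluable subjects do not give the stated 90% power for the Time × Group interaction if d = 0.245 is the post-baseline difference between arms

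*Protocol article*

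**What the plan says.** All references are to the protocol article.

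- **Effect size (8.2.1).** It is taken from "a previous eHealth Literacy study that reported a small-to-moderate effect size (d = 0.245"). The text does not define it further.
- **Design (8.2.1, 8.2.3).** The calculation is made "with five repeated measurements over a 6-month period" (8.2.1), for a "two-arm, prospective, parallel-group (1:1), randomised controlled trial" (8.2.3).
- **Test (8.2.1).** The calculation is for a "repeated-measures analysis of variance to detect a significant between-group interaction effect at 5% significance (G*Power 3.1").
- **Result (8.2.1).** "a total sample size of 108 subjects (i.e., 54 per group) is required to achieve a power of 90" per cent.
- **Attrition (8.2.1).** "assuming an attrition rate of 30% [39], 156 subjects (78 per group) will be recruited for each study".
- **Planned analysis (8.2.4).** The primary outcome is the eHEAL score at baseline and Months 2, 3, 4 and 6. Each continuous outcome gets a linear mixed model with Time, Group and their product. "A significant result of the interaction term (Time × Group") is to be read as a differential change between arms.

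The article gives no Cohen's f, correlation among repeated measures, sphericity correction or G*Power test option, and no conversion from d to an interaction effect.

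**The concern.** A between-group d and the f of a Time × Group interaction are different quantities. For the interaction, f is the standard deviation of the interaction effects across the arm-by-time cells, in units of the outcome SD. Randomised arms are expected to start equal, so a follow-up gap of 0.245 SD produces a much smaller interaction f than 0.245, and smaller also than half of it. A total of 108 subjects is low for 90% power at so small an effect, which suggests that the number came from another effect size, another test, or both.

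The same calculation sizes three separate trials (ethnic minorities, people with chronic illness, caregivers), 3 × 156 = 468 participants. If the power is far below 90%, each trial would more likely than not miss the effect it was sized for, and non-significant results could be misread as evidence that the intervention does not work.

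**Working it through.** **Inputs from the article:** d = 0.245; m = 5 measurements; N = 108 in two equal arms; two-sided 5% level; 30% attrition.

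**Assumptions, because the article gives no values:** correlation ρ (0.5 as base, then varied), compound symmetry with no sphericity correction, time as a category, outcome SD = 1, arms equal at baseline, and d read as the gap between arms after baseline.

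**Step 1. Attrition.** 54 / 0.70 = 77.1, rounded up to 78 per arm, 156 in total. This reproduces.

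**Step 2. Where 108 could come from.** Noncentral F:

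- Interaction: λ = N·m·f² / (1 − ρ), with m − 1 = 4 and 4(N − 2) df.
- Between-group main effect: λ = N·m·f² / (1 + (m − 1)ρ), with 1 and N − 2 df.

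| Route (ρ = 0.5) | N for 90% | Power at 108 |
|---|---|---|
| Main effect, f = 0.245 | 108 | 90.3% |
| Interaction, f = d/2 = 0.1225 | 104 | 91.2% |
| Interaction, f = 0.245 | 28 | >99.9% |
| Main effect, f = d/2 = 0.1225 | 424 | 37% |

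The first route matches exactly: λ = 108 × 5 × 0.0600 / 3 = 10.80. It treats d as if it were f and tests a main effect instead of the interaction. The second is close, but uses an f that a gap of 0.245 does not produce (Step 3). Neither is the planned test at d = 0.245.

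**Step 3. Interaction f implied by d.** With two equal arms, f is half the standard deviation, over the five visits, of the gap between arms.

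- Constant gap (0, d, d, d, d): SD = d × √(0.8 × 0.2) = 0.4d, so f = 0.4 × 0.1225 = 0.049.
- Linear by month (0, 2/6, 3/6, 4/6, 1, times d): f = 0.0408.
- Largest f when the gap stays between 0 and d (for example 0, 0, d, d, d): SD = d × √(0.6 × 0.4) = 0.49d, so f = 0.060.

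**Step 4. Power of the interaction test at N = 108.** For a constant gap at ρ = 0.5, λ = 108 × 5 × 0.049² / 0.5 = 2.59 with 4 and 424 df, giving 21.2%.

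| Pattern | ρ = 0.3 | 0.5 | 0.7 | 0.8 |
|---|---|---|---|---|
| Constant gap | 16% | 21% | 34% | 50% |
| Linear by month | 12% | 16% | 24% | 36% |
| Largest f, gap within 0 to d | 23% | 31% | 50% | 70% |

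A constant gap gives 83% at ρ = 0.9 and passes 90% at about ρ = 0.92. At ρ = 0.5 it needs about 644 evaluable subjects for 90%. With 108 it reaches 90% only at d of about 0.60: f = 0.2 × 0.60 = 0.12, λ = 15.55, power 89.9%. If all 156 were retained, power at d = 0.245 would be 30%.

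**Step 5. A single contrast.** Take the baseline-adjusted difference in the mean of the four follow-ups, with 54 per arm and ρ = 0.5. Residual variance = (1 + 3ρ)/4 − ρ² = 0.625 − 0.25 = 0.375. SE = √(2 × 0.375 / 54) = 0.118.

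- Constant gap: 0.245 / 0.118 = 2.08, power about 55%. For 90%, d = (1.960 + 1.282) × 0.118 = 0.38.
- Linear by month: mean gap = 0.625 × 0.245 = 0.153; 0.153 / 0.118 = 1.30, power about 25%.

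**The case against.** The strongest objections concern what the article leaves open.

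- **How 108 was obtained.** A reader might infer that half of d was entered as the interaction f. The text does not support stating that: no f is given, that route returns 104, and the main-effect route with 0.245 as f returns 108 exactly. The main-effect route cannot be proven either.
- **One power figure.** A reader might take 21% as the power of the trial. It depends on ρ = 0.5, compound symmetry and a flat gap, none of which the article states. The result is a range, and a very high correlation would restore 90%.
- **A ceiling for every pattern.** The 31% at ρ = 0.5 is a maximum only when the gap stays between 0 and d. A gap that reverses sign (0, d, d, −d, −d) gives f = 0.110 and 83%. That is not a pattern an effective intervention would be expected to show, but it rules out an unconditional ceiling.
- **Degrees of freedom.** Section 8.2.4 does not say whether Time is a category or continuous. If continuous, the interaction is a one-degree-of-freedom slope test, so a 4-df test is not established. The slope test has about 23% (constant gap) to 27% (linear) power at ρ = 0.5, so the conclusion does not change.
- **Meaning of d.** The cited study is not available here. Reading d as the gap in outcome SDs is the ordinary reading but remains an assumption.
- **The replacement contrast.** It is a design preference, and its gain shrinks if the effect builds up slowly.

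These points limit the diagnosis and the precision. None restores 90% for the stated test at d = 0.245 under ordinary correlations.

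**Conclusion.** The point holds in a conditional form. If d = 0.245 is the standardised difference between arms after baseline, 108 evaluable subjects do not give 90% power for Time × Group. With equal baselines, compound symmetry and categorical time, power is about 12–34% over constant and linear patterns at correlations 0.3–0.7, and 50% for a constant gap at 0.8. A constant gap needs a correlation of about 0.92 to reach the stated figure. The stated power is therefore wrong for the test and effect named beside it, in all three trials. How it arose cannot be settled from the text. The inflation for attrition to 156 is correct.

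**What to change.** 1. **Restate the power in 8.2.1** for the planned interaction test, giving f and how it follows from d, the assumed correlation, the sphericity correction and the G*Power option. At correlation 0.5 and a constant gap, 54 per arm give 90% only at d of about 0.60.
2. **Preferably, pre-specify one contrast from the same mixed model as the primary test**: the baseline-adjusted difference between arms in eHEAL, averaged over Months 2, 3, 4 and 6. State its power with its assumptions: about 55% at d = 0.245 and 90% at d of about 0.38 for a constant gap at correlation 0.5, but only about 25% at d = 0.245 if the effect builds up linearly to Month 6.

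The cost is one rewritten sample-size paragraph, one analysis sentence if the contrast is adopted, and a less favourable stated power. No extra participants are needed for either change, but neither brings power at d = 0.245 to 90% under these assumptions, and the restated text should say so.

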#### 8.2.2. Methods

A community-based participatory research approach [37] will be adopted in this study by inviting stakeholders (EM adults, PWCI and CGs) to participate in various phases of the study. This participatory method can provide opportunities for relevant stakeholders to share their perspectives on and knowledge of a particular topic (in this study, their ability to access, understand and interpret health information from the Internet or social media) with the research team and contribute their experiences to the development of learning objectives and materials in the DHL interventions. In this collaborative research process, the stakeholders will work with researchers to identify issues that are critical to their communities; identify resources and solutions; and develop, implement and evaluate interventions. We intend to engage the stakeholders in various research processes to understand and address their concerns. The materials of the interventions will be developed ‘*in context*’, i.e., where stakeholders easily find them relevant to their daily lives. This co-creation of new knowledge by stakeholders and researchers will increase the uptake of the research outcomes and adoption of the DHL interventions.

#### 8.2.3. Study Design

Phase 1. Each qualitative study will include three to five focus group interviews and five cognitive interviews. In the focus group interviews, the stakeholders will be encouraged to indicate their problems and concerns about DHL, propose resources/solutions and formulate a plan. Version 1 of the interventions will be based on these comments. Cognitive interviews will be conducted with the stakeholders when the version 1 interventions are available. Here, we will ask the stakeholders to go through the interventions step-by-step to evaluate their flow and content.

Phase 2. A feasibility and acceptability study with individual interviews will be conducted to collect views from 20 stakeholders and two moderators. The moderators will be the trained workers who facilitate online group discussions on social media platforms.

Phase 3. This will be a two-arm, prospective, parallel-group (1:1), randomised controlled trial.

Settings. Participants will be recruited from non-governmental organisations that provide services to EMs, PWCI and CGs.

Interventions. ‘Self-determination Theory’ will be used to guide the development of the intervention. That is, we address ‘autonomy, competence and connection (or relatedness)’ when we develop the intervention. While we are inviting the stakeholders (EM, PWCI, CG) to co-create the intervention with us, we ascertain they feel in control of their own behaviours and goals (whether they are determined to do the best to prevent COVID-19). We will also support them to gain mastery of tasks and learn different skills. Additionally, we will make sure the stakeholders experience a sense of belonging (attachment) to the materials we develop. The interventions will be developed based on the Best Practices for Digital Health Literacy [40], WHO health literacy toolkits [41] and the findings of the interviews in Phase 1. The content to be covered in the intervention will include news about vaccines; alerts about COVID-19 preventive measures; guidelines on social distancing, COVID-19 screening test arrangements, vaccination and compulsory quarantines; COVID-19–related law enforcement; and self-monitoring of COVID-19 symptoms. The interventions will be designed for three social media and communication platforms (a closed Facebook Social Learning Group, YouTube and Viber/ WhatsApp). Facebook and YouTube were chosen because they are the top two social media platforms in HK (used by 82% and 81% of users in HK, respectively) [42]. The ‘Social Learning Group’ in Facebook is a closed system that protects participants’ privacy, and it serves as the key platform for learning the short-clip videos our group developed for a different study [43], including step-by-step instructions from the moderators, eight online exercises and eight interactive sessions. The videos will be co-developed with representatives of the respective ethnic groups in six languages (English, Indonesian, Hindi, Nepali, Urdu and Cantonese), uploaded to YouTube and shared in the Facebook Social Learning Group. Development of the intervention will also consider the latest situation of COVID-19 regarding the content and the mode of delivery of preventive measures and vaccination recommendations. PWCI and CGs require different types of health information; for example, PWCI need information about the contraindications of vaccination to the long-term drugs they are taking, whilst CGs need information about the latest policies regarding visit restrictions or vaccination arrangements for residential care homes. Both groups will be invited to participate in the development of the intervention.

Procedures. This online learning programme will be operational for 6 months (eight weekly sessions in months 1 and 2 and three interactive booster sessions in months 3 to 6). Before using Facebook, a 1 h virtual or face-to-face training session will be provided to the participants to familiarise themselves with all of the features on Facebook and the privacy settings. Communication tools that enable end-to-end message encryption, such as Viber or WhatsApp, will be used for communication within small groups (six to ten participants supported by a trained moderator). Viber is the most common communication tool used by the Nepalese population, and WhatsApp is often used by Pakistani, Filipino, Indonesian and Chinese populations. Virtual bi-weekly group meetings (30 min each) will be held via group video calls in WhatsApp or Viber. In a pilot study [31], the participants recommended that the learning period be extended to 8 weeks plus some booster sessions in subsequent months. The fidelity of the intervention will be assessed by a trained research assistant who retrieves the record in the backend of the Facebook Social Learning Group and assesses the use of the materials by the participants, the duration of interactions among the participants and with the moderator, and the frequency of the use of materials in discussion. The process of the proposed study is shown in Figure 4.

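### Study 2 delivers its intervention in moderated groups of six to ten, but the sample size makes no allowance for this and the described model names no delivery-group term

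*Protocol article*

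**What the plan says.** All references are to the Protocol article.

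- **Allocation (8.2.3, Phase 3).** "This will be a two-arm, prospective, parallel-group (1:1), randomised controlled trial". Section 8.2.1 has 156 people per population randomised to intervention or control. No cluster randomisation is described.
- **Delivery (8.2.3, Procedures).** Communication takes place in "small groups (six to ten participants supported by a trained moderator"). "Virtual bi-weekly group meetings (30 min each) will be held via group video calls in WhatsApp or Viber". The programme runs for six months.
- **Sample size (8.2.1).** The source study "reported a small-to-moderate effect size (d = 0.245"). Outcomes are measured five times in six months. On that basis, "a total sample size of 108 subjects (i.e., 54 per group) is required to achieve a power of 90" per cent, using a repeated-measures ANOVA "to detect a significant between-group interaction effect at 5% significance (G*Power 3.1"). The only inflation is for 30% attrition, which gives 156.
- **Analysis (8.2.4).** "we will perform separate linear mixed-effects models for each of the continuous outcomes". The terms named are time, group and their interaction, where *group* is the trial arm. A significant interaction is the criterion for a difference between arms.

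Two sister trials in the same article do allow for clustering. Study 1 (7.2.1) assumes an ICC of 0.01. Study 5 (11.2.1 and 11.2.3) uses 0.05 with a three-level model.

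**The concern.** This has the structure of an individually randomised group-treatment trial. People enter separately, but those in the intervention arm then share a moderator, a chat group and regular calls for months. Interaction among them is part of the design: the guiding theory in 8.2.3 targets relatedness, and fidelity is scored partly on how long participants interact with one another and with the moderator. Some similarity in how members of a group change is therefore plausible.

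If that similarity exists, the mean change in the intervention arm is less precise than the same number of independent people would give. An analysis that ignores it produces intervals that are too narrow and p-values that are too small. That applies to the primary outcome (eHEAL) in all three populations. A sample size that ignores it overstates power.

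**Working it through.** **Inputs from the article:** group size m = 6 to 10; d = 0.245; five measurements; N = 108; two-sided 5%; 90% power; 30% attrition.

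**Assumptions, not in the article:** repeated-measures correlation ρ = 0.5; ICC of change of 0.01, 0.05 or 0.10; clustering in the intervention arm only, because the control condition is not described. The first two ICCs are those used for Studies 1 and 5. The third is a higher value added to show the range.

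**1. Reproduce the stated sample size under independence.** Take f = d/2 = 0.1225 and λ = f² × N × 5/(1 − ρ).

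- λ = 0.1225² × 108 × 5/0.5 = 16.2, with 4 and 4 × (108 − 2) = 424 degrees of freedom. Power is 0.912.
- With f rounded to 0.12, power at 108 is 0.899.
- Attrition: 54/0.70 = 77.1, so 78 per arm and 156 in total.

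The stated figures are therefore what independence gives, with essentially no room for a design effect. One caution: 108 also comes out of the between-factors option with f = 0.245 and ρ = 0.5 (power 0.903), so the article alone does not settle which option was used. Neither route contains a clustering allowance.

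**2. Inflation when delivery groups are ignored.** Intervention-arm design effect DE = 1 + (m − 1) × ICC. Variance ratio of the contrast r = (DE + 1)/2. True level = 2 × [1 − Φ(1.96/√r)].

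Example, m = 8 and ICC = 0.05: DE = 1.35, r = 1.175, √r = 1.084, true level 7.1%.

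| ICC | m = 6 | m = 8 | m = 10 | true SE / model SE |
|---|---|---|---|---|
| 0.01 | 5.3% | 5.4% | 5.5% | 1.01–1.02 |
| 0.05 | 6.5% | 7.1% | 7.7% | 1.06–1.11 |
| 0.10 | 8.0% | 9.2% | 10.4% | 1.12–1.20 |

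**3. Check on the test actually planned.** The formula in step 2 is for a single contrast, whereas the decision rule is a 4-degree-of-freedom interaction. Simulating that test (54 and 78 per arm, m = 8, group effect present after baseline only, 6,000 runs each) gave:

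- ICC 0: 4.8–5.1%
- ICC 0.01: 5.2–5.3%
- ICC 0.05: 6.5–6.6%
- ICC 0.10: 8.0–8.9%

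These are close to the m = 8 column and a little below it at the higher ICCs.

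**4. Power at N = 108 once clustering is respected.** Replace f by f/√r, with m = 8. This is approximate, because it applies the average variance ratio.

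| ICC | power at 108 | N for 90% | recruited at 30% attrition |
|---|---|---|---|
| 0.01 | 0.902 | 108 | 156 |
| 0.05 | 0.856 | 122 | 176 |
| 0.10 | 0.798 | 140 | 200 |

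**5. Which random effect matters.** Suppose a member of delivery group g carries a constant effect b at every visit. Follow-up minus baseline is then (… + b) − (… + b), and b drops out. In complete, balanced data a time-constant group intercept therefore leaves the time-by-arm test unchanged. The component that inflates this test is a group effect that appears after baseline, that is, group by time.

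**The case against.** **The analysis section may simply be condensed.** It lists fixed effects and no random effects at all, not even one for participant, which a mixed model of five repeated measures would normally have. A reader might infer that the model excludes delivery groups. The article does not say so; it only fails to name such a term. This objection stands for the model. It does not remove the point, because the sample-size calculation is stated in full and contains no clustering allowance, unlike those of Studies 1 and 5.

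**The inflation is conditional.** A reader might infer that false positives certainly exceed 5%. That needs a positive within-group ICC of change, and Study 2 gives none. At 0.01 the effect is negligible. The 10% figure needs both the largest group size and ICC 0.10. This objection stands in full.

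**Details that cannot be leaned on.** It is tempting to add that small groups are formed by language. Section 8.2.3 says only which messaging application each population tends to use. Language is also a baseline trait found in both arms, so it is not clustering created by the intervention. Likewise, clustering in one arm only is an assumption. If controls also met in groups of 8, the levels would be 5.8%, 9.2% and 13.3% at ICCs of 0.01, 0.05 and 0.10.

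**Conclusion.** The point holds in conditional form. The sample size ignores group delivery, and the described model names no term for it. If the ICC of change within delivery groups is positive, the planned interaction test, run as described, is too liberal and the stated power is too high.

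Across the ICCs this programme itself uses (0.01 to 0.05), the true level is about 5.3–7.7% for groups of 6 to 10. With groups of 8, power at 108 is about 90% to 86%. At ICC 0.10 the level is about 8–10% (8–9% in the simulated 4-degree-of-freedom test with groups of 8) and power is about 80%. These figures rest on an assumed ICC, clustering in the intervention arm only and, for power, ρ = 0.5.

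Confidence is high that the sample size makes no allowance and moderate about the size of the effect. It should be corrected, but it does not undermine the trial.

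**What to change.** 1. Record each participant's delivery-group identifier from the outset. If it is not recorded at delivery, it may not be recoverable later.
2. Specify a partially nested mixed model. Its essential component is a delivery-group random effect on post-baseline change (group by time) in the intervention arm. A time-constant group intercept may be added but is not sufficient alone.
3. Treat each control as a singleton, unless controls also meet in groups. State which applies.
4. Use Kenward-Roger or Satterthwaite degrees of freedom. With 78 in the intervention arm there would be only about 8 groups (78/10 = 7.8) to 13 groups (78/6) per population.
5. Restate the power for 108 analysed and 156 recruited over a stated ICC range, and say whether the resulting power is acceptable or the sample should grow.

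The cost is one identifier and a further variance component, slightly wider intervals and a slightly lower stated power. Enlarging the sample is a separate decision. Under the assumptions above, keeping 90% power would take about 176 recruited per population at ICC 0.05 and about 200 at 0.10.
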